### Biomarker

2.13

Peripheral NSE will be used to test the potential injury of neuron. Ten milliliters of venous blood are adopted from each participant into an anticoagulant‐free vacuum tube. The blood will be immediately centrifuged at 4000 × *g* for 10 min, and serum is kept frozen at −80°C until analysis. NSE levels are measured with electrochemiluminescence assay, using a commercial kit conforming to the manufacturer instructions (Roche Diagnostics, Mannheim, Germany) and data will be shown in ng/ml.

### Data management

2.14

Data will be entered into OpenClinica online with range check. The academic board of Tianjin Anding Hospital will in charge of overseeing the trial including data monitoring, endpoint adjudication, and project implementation, which will be independent from investigators and the sponsor.

### Medication use

2.15

None.

### Side effects

2.16

None.

### Safety reporting: Adverse events/serious adverse events

2.17

It is a cross‐sectional study without any interventions, and all assessments will occur during euthymic state. So, there is no need for AE/SAE monitoring based on the design of the study.

### Withdrawal of subjects

2.18

Subjects can quit the study at any time for any considerations without any consequences. The investigator can decide to withdraw subjects from the trial if the subjects are not compliant with the study procedures or any conditions emerge that violate the inclusion/exclusion criteria during processing. All withdrawals will be excluded from the study and new participants will be recruited.

### Statistical analysis

2.19

The data obtained from questionnaires and basic information are expressed in “mean ± standard deviation” in the case of normal distributions and in median and quartile in the case of nonnormal distributions. The comparisons in scores of each scale between two groups will be made by Covariance Analysis; the Chi Square and Analysis of Variance (ANOVA) test will be used to test the consistency of match between groups for factors such as age, sex, MADRS scores, YMRS scores, PAS scores, use of mood stabilizers, age of onset, number of attacks, and so forth, and the factors with significantly different distributions between two groups will be used as covariates. Furthermore, the two groups of patients will be combined as a whole and then Multiple Linear Regression equations will be used to analyze the linear relationship between each factor and neurocognitive function. The test level is α = 0.05.

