### Sample size calculation

2.6

There are no data available on effect size and standard deviations specific for cognitive function of targeted patients, therefore power calculation remains speculative. For the value of *δ*, we assume that it should come out between 0.25 and 0.5, and we set it as 0.3. With formula *n*
_1_ = *n*
_2_ = 2 × [(*t*
_α/2_ + *t*
_β/2_) *S*/*δ*]^2^, setting *α* at 0.05 and *β* at 0.20 in a two‐tailed independent *t*‐test indicated that a minimum of 62 patients per group is needed (totally 124 participants).

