### Study endpoint

2.7

Main study endpoints include neurocognitive functioning, which can be assessed by:
Subjective cognitive measures: The Cognitive Complaints in Bipolar Disorder Rating Assessment (COBRA) (Rosa et al., 2013).Objective cognitive measures: The Stroop Color and Word Test (SCWT) (Golden, 1978), the categorical verbal fluency test (CVFT) (animal naming) (Chen et al., 2000), Chinese Auditory Verbal Learning Test (C‐AVLT) (Lee et al., 2002), and the Trail Making Test Part B (TMT‐B) (Lu & Bigler, 2000); the Digital Span Forward and Backward subtest (DSFB) and the Digit Symbol Coding subtest (DSC) of the Wechsler Adult Intelligence Scale‐Revised by China (WAIS‐RC) (Gong, 1982) and Trail Making Test Part A (TMT‐A) (Lezak et al., 2004); and the Visual Reproduction subtest (VRP) and the Visual Recognition subtest (VRC) of the Wechsler Memory Scale‐Revised (WMS‐R) (Gong, 1987).

Secondary study endpoints are as follows: Global Assessment Function (GAF), Methods Checklist on Quality of Life issued by World Health Organization‐Brief version (WHOQOL‐BRIEF), Pittsburgh Sleep Quality Index (PSQI), Positive and Negative Affect Scale (PANAS), and neuron‐specific enolase (NSE).

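### Ten main cognitive endpoints are each compared at α = 0.05 with no primary or correction, so the chance of at least one false difference rises from 5% to about 29–40%

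*Protocol article*

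**What the plan says.** Section 2.7 (Study endpoint) opens its list in the plural: "Main study endpoints include neurocognitive functioning, which can be assessed by". It then names one subjective measure, COBRA, and nine objective ones: SCWT, CVFT, C-AVLT, TMT-B, DSFB, DSC, TMT-A, VRP and VRC. It gives no single primary, composite or order of testing.

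Section 2.19 (Statistical analysis) takes the single scale as the unit of testing: "The comparisons in scores of each scale between two groups will be made by Covariance Analysis". It adds multiple linear regressions of neurocognitive function on each factor in the pooled sample, and closes with one level for everything: "The test level is α = 0.05". The article mentions no multiplicity adjustment.

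Section 2.6 (Sample size calculation) is built on one two-tailed independent t-test, "setting *α* at 0.05 and *β* at 0.20", and arrives at 62 patients per group.

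The Background calls the study mainly explorative. In the same sentence it says that the authors expect early antidepressant treatment to affect neurocognitive function negatively.

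**The concern.** The study is sized for one comparison, but ten main comparisons will be run and nothing says which one answers the question. There is also no rule for what counts as a positive result, such as one significant test, most of them, or a particular one. Because a direction is stated in advance, one significant test out of ten could be reported as support for the expected harm, although its error rate would not be the nominal 5%. The abstract says the results are expected to guide prevention and treatment of bipolar disorder, so the error rate behind a main finding matters. A primary endpoint chosen after the results are seen could not restore it.

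**Working it through.** **Inputs from the protocol article.** Ten main instruments (section 2.7); α = 0.05 for each comparison (2.19); two-tailed test, β = 0.20, δ = 0.3 and 62 per group (2.6). **Assumed, because the article gives no value:** the correlation between the test statistics, taken as equal for all pairs, and the standard deviation S.

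**1. The stated sample size.** The usual form of the formula is n = 2[(1.960 + 0.842)S/δ]².
- With δ = 0.3 and S = 1, n = 174.4, so 175 per group and not 62.
- Solving for n = 62 gives S = 0.3 × √31 / 2.802 ≈ 0.596, a standardised difference of 0.3/0.596 ≈ 0.50.
- Section 2.6 gives no S and concedes: "There are no data available on effect size and standard deviations specific for cognitive function of targeted patients". The 62 therefore cannot be reproduced from the stated inputs, which does not prove it wrong. What matters here is that it is a one-test figure at α = 0.05. Power is shown below for both 0.3 SD and 0.5 SD.

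**2. Familywise error over ten tests, no true difference on any.**
- Independent, either direction: 1 − 0.95¹⁰ = 0.401.
- Independent, harm direction only (0.025 per test): 1 − 0.975¹⁰ = 0.224.
- Correlated: simulation of equicorrelated normal test statistics, each compared with ±1.96.

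| Assumed correlation | Any false difference | False difference in the harm direction |
|---|---|---|
| 0 | 40% | 22% |
| 0.3 | 35% | 18% |
| 0.4 | 32% | 16% |
| 0.5 | 29% | 14% |
| 0.7 | 21% | 11% |
| One test, for reference | 5% | 2.5% |

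Scoring digit span forward and backward separately makes eleven tests: 1 − 0.95¹¹ = 43% if independent.

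**3. What correction costs at 62 per group (two-sided t-test).** The first Holm step over ten tests uses 0.05/10 = 0.005.

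| Assumed effect on one test | Power at 0.05 | Power at 0.005 |
|---|---|---|
| 0.3 SD | 38% | 12% |
| 0.5 SD | 79% | 47% |

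**4. What a composite would do.** The mean of nine z-scores with pairwise correlation ρ has SD √((1 + 8ρ)/9), which is 0.615, 0.683 and 0.745 at ρ = 0.3, 0.4 and 0.5.
- All nine tests shifted by 0.3 SD: the composite effect is 0.3 divided by that SD, or 0.49, 0.44 and 0.40, with power of 77%, 68% and 60%.
- Only three of the nine shifted by 0.3 SD: the mean shift is 3 × 0.3/9 = 0.1, and power is 15%, 13% and 11%. That is below the 38% for one affected test taken alone.

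**The case against.** **The study is called explorative.** This bears on severity but does not settle the matter. The sentence that carries the label also states a directional expectation, and section 2.6 sizes a conventional two-tailed test.

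**An analysis plan that is not shown may deal with multiplicity.** It may, and section 2.19 does not use the word unadjusted. But the article fixes both the set of main endpoints and the level for comparing them. A plan that named a primary or divided α would change what sections 2.7 and 2.19 say. The mismatch between one sized test and ten main ones is in the article itself.

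**Cognitive tests are correlated, so 40% is an upper figure.** For ten tests this is right. Positive correlation lowers the figure, to 21% at 0.7, which is still about four times the nominal level.

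**A reader might infer that a false finding of harm is likely.** The numbers do not support that. The 29–40% counts false differences in both directions, including apparent benefit. In the harm direction alone the range is 14–22%.

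**A reader might also infer that a composite is the only sound repair.** It is not. Its advantage assumes a similar effect on every test. The article's Background and Discussion cite deficits in particular domains (visual and working memory) and also antidepressant benefits on psychomotor speed and delayed recall. Effects confined to some domains are diluted in a mean z-score, and opposing effects cancel.

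**Conclusion.** The point stands. As written, the plan runs ten main comparisons at 0.05 each on a sample sized for one, with no primary endpoint or correction. The chance of at least one false difference is 40% under independence and 29–35% at correlations of 0.5 to 0.3. In the harm direction alone it is 22% under independence and 14–18% at those correlations, against 2.5% for one test: a clear inflation, but not a likely event.

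These figures hold for ten tests with no true difference on any, and for equal pairwise correlations, which are assumed. They exclude confounding, which is a separate matter in this observational design. All power figures depend on an assumed standardised effect, because section 2.6 gives no SD.

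**What to change.** Before the data are analysed:

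1. **Section 2.7:** name one primary cognitive endpoint, tested at two-sided 0.05. One option is the mean z-score of the nine objective tests, each signed so that higher is better. A single pre-named test would also serve.
2. **Section 2.12, if a composite is used:** settle the scoring directions first. The section says that higher CVFT scores mean worse functioning, while section 2.7 describes that test as animal naming. The sign must be confirmed before the test enters a sum.
3. **Section 2.19:** report the remaining cognitive tests and COBRA with Holm-adjusted p-values. If no primary is named, apply Holm to all ten.
4. **Section 2.19:** label the regressions on each factor exploratory.

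This costs some rewording and needs no new patients, visits or measurements. The price is statistical. A composite dilutes or cancels domain-specific effects, and Holm-adjusted single tests will often miss them: power at the first step is about 12% for 0.3 SD and 47% for 0.5 SD, both assumed effects. The choice of primary should therefore rest on which domains the investigators expect to be affected.

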## Abstract

**Objectives:**

Patients with bipolar disorder (BD) have a wide range of neurocognitive dysfunction even in euthymic state, leading to impaired psychosocial function and reduced quality of life. However, the understanding on risk factors related to neurocognitive impairment in such group of people is limited. In view of significantly delayed diagnosis of BD and common use of antidepressants prior to the BD diagnosis, the study aims to clarify whether systemic antidepressant use in early stage, defined as from the initial depressive episode to the diagnosis of BD, could impact neurocognitive function of euthymic bipolar patients.

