About 50% of BD initiates its expression in the form of depressive episode (Drancourt et al., 2013; Tondo et al., 2010), in which only 20% can get a diagnosis of BD within the first year of onset (Hirschfeld et al., 2003), and the average delay from first episode to diagnosis of BD is 5–10 years (Baldessarini et al., 2007). The main reason for this significant delay is that a large number of bipolar patients do not experience any manic/hypomanic symptoms in the early stage, defined as a term from initial depressive onset to the diagnosis of BD, and the clinical manifestations of bipolar depression are highly similar to unipolar depressive episodes (Drancourt et al., 2013; Tondo et al., 2010). As a result, patients may receive systemic treatment with antidepressants for a long time because of the misdiagnosis or delayed diagnosis. The attitude regarding the effect of antidepressants used in early stage on neurocognitive function of patients with BD is controversial yet. Empirically, antidepressant treatment could deprave the natural course of disease and facilitate switching from depressive onset to episodes of mania, hypomania, or mixed state (Berkol et al., 2019; Sole et al., 2017; Viktorin et al., 2014), which may cause cognitive injury (Goodwin et al., 2008). For example, BD patients with higher number of manic and/or hypomanic episodes had a worse performance in Neurocognitive Composite Index (NCI), visual memory, and working memory (Sánchez‐Morla et al., 2019); furthermore, patients with BD, particularly those with multiple mood episodes, showed severe dysfunction in emotional memory than healthy controls (Fijtman et al., 2020). In addition, the number of manic episodes was positively correlated with level of 8‐hydroxy‐2 deoxyguanosine (8‐OHdG), a modulator of DNA methylation, which could be a potential mechanism underlying cognitive dysfunction (Soeiro‐de‐Souza et al., 2013). Consistently, studies have shown that antidepressant agents per se undermined the neurocognitive function of the elderly and increased the incidence of mild cognitive impairment or dementia (Leng et al., 2018; Moraros et al., 2017), which may contribute partly to the neurocognitive impairments in patients with BD. However, it is arguable to expand the view based on the evidence from bipolar depression to depressive episode prior to any mania/hypomania emergence. Furthermore, it has been illustrated that antidepressant treatment can improve cognitive performance (Brendel et al., 2018; Tunc‐Ozcan et al., 2019), although the evidence did not derive from studies focusing on bipolar patients specifically. In view of the high incidence of delayed diagnosis or misdiagnosis of BD (Tondo et al., 2010), the use of antidepressants in the early stage is quite common and extensive. Therefore, a further understanding in the relationship between antidepressant used in the early stage and neurocognitive function of bipolar patients has significantly scientific and clinical significance.

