
The current study attempts to clarify this question by making comparisons in neurocognitive function between bipolar patients who had a depressive episode as initial onset and being with and without systemic antidepressant treatment (received adequate dosage of antidepressants for 6 weeks at least) in early stage. Furthermore, the social functions and quality of life will also be investigated because both items are highly associated with cognitive functions and are indicative for functional rehabilitation. Apart from those, we will also study the influence of antidepressants used in early stage on impulsiveness, quality of sleep, and positive and negative affect. Lastly, peripheral neuron‐specific enolase (NSE) will be evaluated. NSE, a cell‐specific isoenzyme of glycolytic enolase, is known as a sensitive marker of neuronal damage (Isgrò et al., 2015). It has been showed that high level of serum NSE was related to mild cognitive dysfunction in patients with diabetic retinopathy (Yu et al., 2020) and that serum NSE levels of BD patients were significantly different from healthy controls (Akcan et al., 2018). In this regard, it is expected to examine the potential association between serum NSE level and cognitive function of BD patients. Finally, although it is mainly an explorative investigation and is informative for clinical practice regardless of outcomes, we expect that systemic antidepressant treatments in early stage could negatively affect the neurocognitive function, social functions, and quality of life of patients with BD.

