### Additional study parameters

2.9

The information on age, sex, nation, family history of psychiatric disorder, age of onset, time of BD diagnosis, education level, use of mood stabilizer in early stage, number of depressive and manic episodes, history of euthymia (yes/no), and premorbid adjustment ability will be collected.

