## DISCUSSION

3

Regarding the critical role of cognitive impairment in psychosocial disability and poorer quality of life, improving cognitive function has become a crucial goal in the management of BD patients. In this regard, increasing amount of research examining pharmacological and psychotherapeutic treatments was performed during the past decade (Alda et al., 2017; Solé et al., 2015). The research outcomes are inconsistent and no therapeutic intervention with sufficient efficacy is well‐established for improving cognitive dysfunction of BD yet (Miskowiak et al., 2016), although some of psychotherapeutic treatments or drugs appear as promising candidates. Many factors contributed to the discrepant outcomes such as poor randomization procedure, age of onset, number of depressive and manic episodes, severity of symptoms, and medications used specifically. In view of significantly delayed diagnosis of BD and common use of antidepressants in early stage, the effect of antidepressant agents on cognitive function has attracted increasing attention. But the data are still relatively rare, and the evidence is controversial. For example, a meta‐analysis estimated the relationship between antidepressant use and cognitive impairment and found that the odds of cognitive impairment were positively associated with antidepressant use in participants with an average age equal to or more than 65 years (odds ratio [OR] = 1.65), whereas those with participants aged less than 65 revealed an even stronger association (OR = 3.25) (Moraros et al., 2017); and also the study by Leng and colleagues illustrated that users of selective serotonin reuptake inhibitors and trazodone were as more as two to three times to develop dementia compared with the nonusers 5 years later, although the use of tricyclic antidepressants or other antidepressants was not involved in cognitive impairment (Leng et al., 2018). The evidence above suggests that antidepressant use could be a contributor for cognitive impairment of patients with mood disorder. Importantly, it is believed empirically that antidepressant treatment could deprave the natural course of BD and switch from depressive episode to episode of mania, hypomania, or mixed state (Viktorin et al., 2014), which may undermine the cognitive performance of bipolar patients (Goodwin et al., 2008). For instance, it was found that the higher number of manic and/or hypomanic episodes was negatively correlated with the cognitive performance of euthymic BD patients (*n* = 99) such as NCI, visual memory, and working memory in a 5‐year follow‐up longitudinal study (Sánchez‐Morla et al., 2019); furthermore, BD patients (*n* = 33), especially those with multiple mood episodes including mania, hypomania, and/or mixed state, showed severe impairments in emotional memory than healthy controls (*n* = 20) (Fijtman et al., 2020). Considering the significantly delayed diagnosis of BD and common use of antidepressants in clinical practice, such potential scathing effects should gather more attention. In contrast, another meta‐analysis suggested that antidepressants played a significant positive role in promoting psychomotor speed and delayed recall, with no significant difference between diverse types of antidepressants (Rosenblat et al., 2015). This is in line with the evidence from preclinical research that antidepressant agents could promote executive function and environmental information processing through integrating newborn neural cells into the hippocampal dentate gyrus (Tunc‐Ozcan et al., 2019). However, these data rarely came from clinical trial specifically focusing on the use of antidepressants in bipolar patients in early stage. To this end, the current study aims to clarify this issue by examining the cognitive function between bipolar patients who initiated with depressive episode and being with and without systemic antidepressant treatments in early stage. Additionally, the contemporary management of disease not only requires symptomatic relief but also pursues functional rehabilitation. Therefore, we will also examine the effect of antidepressant treatments in early stage on global function and quality of life of participants because both aspects are highly associated with cognitive function. Considering the potential influence of antidepressant use on progressing of course, the information on sleep quality and positive and negative affect will also be collected. Finally, the peripheral level of NSE will be tested to explore the potential biological mechanism of cognitive impairment.

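### The covariate rule in 2.19 can adjust the main AT versus NT comparison for episode count, removing whatever part of the antidepressant effect acts through episodes and letting a significance test choose the estimand

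*Protocol article*

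**What the plan says.** The aim in the Abstract is to learn whether systemic antidepressant use between the first depressive episode and the diagnosis of BD "could impact neurocognitive function of euthymic bipolar patients". The Background expects that it "could negatively affect the neurocognitive function, social functions, and quality of life of patients with BD". Neither sentence limits the question to an effect that is independent of later episodes.

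Section 2.19 gives the main method: "The comparisons in scores of each scale between two groups will be made by Covariance Analysis". Candidate covariates are screened by group comparison; the list ends with "age of onset, number of attacks, and so forth, and the factors with significantly different distributions between two groups will be used as covariates". No comparison without this adjustment is described.

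Section 2.9 collects the "number of depressive and manic episodes", with no time window and no split at the start of antidepressant treatment.

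The Background states that "antidepressant treatment could deprave the natural course of disease and facilitate switching from depressive onset to episodes of mania, hypomania, or mixed state", says that this may injure cognition, and gives as its first example the poorer test performance of patients with more manic or hypomanic episodes. The Discussion repeats the argument about switching, "which may undermine the cognitive performance of bipolar patients".

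**The concern.** A variable that exposure can change, and that in turn affects the outcome, is an intermediate. Adjusting for it takes the indirect part out of the group contrast. On the protocol's own reasoning, manic, hypomanic and mixed episodes are such a variable, and 2.19 makes their count eligible for the main model.

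The significance trigger adds a second problem. If episode counts do not differ significantly, the contrast estimates a total effect. If they do, it estimates an effect net of episodes. The switch is most likely when treatment has altered the number of episodes, so the plan tends to discount the harm that the authors expect just when the proposed mechanism is at work. A reader of the results would see one label, the effect of systemic antidepressant treatment, for two different quantities.

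**Working it through.** **Timing and direction, from the text.** Every patient starts with a depressive episode (2.4). The exposure window runs from that onset to the diagnosis of BD (Background). Episodes after diagnosis therefore follow the window, and manic or hypomanic episodes can follow treatment within it. The Background supplies both links: antidepressant to episodes, and episodes to cognition.

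**The plan's own figure.** The plan gives no number for episodes. The 62 per group is used here only as an input. With S = 1, two-sided alpha 0.05 and power 0.80, n = 2 × [(1.96 + 0.84)/δ]² gives 175 per group at δ = 0.3 and 63 at δ = 0.5. So 62 does not follow from the stated 0.3 unless S is about 0.60, which 2.6 does not state. That is a separate matter, and the present point does not depend on it.

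**Assumptions for the illustration (the documents give none of these).** Both variables have within-group SD 1, and there is no confounding. AT patients have a = 0.5 SD more episodes. Each SD of episodes changes cognition by b = -0.4 SD.

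1. Total effect = direct effect + a × b. The indirect part is 0.5 × (-0.4) = -0.2.
2. Chance that episode count is selected at p < 0.05: the noncentrality is 0.5 × √(62/2) = 2.78, which gives about 79%.
3. When the count is selected, the adjusted contrast averages the direct effect alone. When it is not, the contrast keeps whatever indirect effect that sample shows. Simulation of the rule at 62 per group combines the two cases:

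| Total effect | Direct effect | Mean estimate under the rule | Power, unadjusted | Power, under the rule |
|---|---|---|---|---|
| -0.5 | -0.3 | about -0.32 | about 79% | about 45% |
| -0.3 | -0.1 | about -0.12 | about 38% | about 12% |
| -0.2 | 0 | about -0.02 | not needed | not needed |

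Repeat runs with other random seeds move the power figures by one or two percentage points.

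**Range over the episode difference** (total -0.5, b = -0.4). At 0.3 SD the count is selected in 38% of studies, the estimate averages -0.43 and power is 67%. At 0.8 SD the figures are 99%, -0.18 and 18%.

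**Range over the mediated share** (total -0.5, episode difference 0.8 SD, b = -0.5 × share/0.8):

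| Share through episodes | Mean estimate | Power |
|---|---|---|
| 0% | -0.50 | 0.72 |
| 25% | -0.38 | 0.50 |
| 50% | -0.25 | 0.27 |
| 75% | -0.12 | 0.11 |
| 100% | 0.00 | 0.05 |

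Without adjustment, the estimate stays near -0.50 with power about 0.79 throughout.

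**The case against.** **Confounding.** The strongest reply is that leaving episode count out is not safe either. This is an observational comparison, and more depressive episodes before diagnosis may make a six-week course of antidepressants more likely. Suppose the same 0.5 SD difference arose wholly before exposure and treatment had no effect. The unadjusted contrast would average 0.5 × (-0.4) = -0.20. The noncentrality is 0.2 × √31 = 1.11, so false positives would run at about 20% instead of 5%. This stands: the count mixes depressive with manic episodes and may include some that precede treatment, so simply deleting it is not a clean remedy.

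**Adjustment removes the effect under study.** A reader might infer this, but the documents do not support it. The Background also proposes harm from the drugs themselves, and its sentence on the expected result names no mechanism. In the first illustration 0.32/0.50 = 64% of the effect remains. Near-total loss needs a direct effect of zero.

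**The count is a lifetime count at assessment.** A reader might infer this too, but neither 2.9 nor 2.19 states a window.

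**Favourable numbers.** A total effect of -0.5 is the top of the range in 2.6, where 0.3 was chosen. This is fair, and the -0.3 row is shown for that reason. At S = 1 that setting has low power even before any adjustment.

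**Exploratory study, unseen SAP.** The Background calls the work mainly explorative, and a separate analysis plan may exist. Neither answers the point, because 2.19 states the rule outright for the main comparison.

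**Conclusion.** The concern holds in limited form. The rule in 2.19 can take out of the main contrast the part of the effect that acts through episodes, and it lets a significance test decide which effect is estimated. The loss lies anywhere between none and all, according to the mediated share. In the -0.5 illustration, with a mediated share of 0.2/0.5 = 40%, the estimate shrinks by about 36% (0.18/0.50).

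The figures rest on an assumed episode difference, an assumed slope and no confounding. They show the mechanism and its scale and do not forecast this study's result. What needs no assumption is that the estimand is not fixed in advance and that the protocol's own reasoning places at least some of the episodes downstream of treatment.

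**What to change.** In 2.19:

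- Replace the significance-triggered rule with covariates fixed in advance from factors that precede early-stage antidepressant treatment, for example age, sex, PAS score and age of onset.
- Make the model without episode counts that can follow exposure (manic or hypomanic episodes, and any episodes after the diagnosis of BD) the main estimate of the total effect.
- Report the episode-adjusted model beside it, labelled as an effect net of episodes.
- Keep episode count in the pooled regression, which is meant to examine each factor, but give its antidepressant coefficient the same label.

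This does not require discarding MADRS and YMRS scores. Their role should also be set in advance and not left to a test.

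The cost is a change of wording and one more model per outcome. Section 2.9 already collects depressive and manic counts and the time of diagnosis; the addition is to record which episodes came before and after diagnosis. The real downside is that early depressive episodes may confound and their dating rests partly on recall. NT patients also have no natural index date from which to count pre-treatment episodes. The two models should therefore be read together as a sensitivity pair. If they disagree, the data alone cannot say how much of the gap is mediation and how much is confounding.
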